### Participant timeline {13}

Figure 1 describes the participant timeline.

**Fig. 1 Fig1:**
[figure not shown]
Participant timeline of the PARTIAL trial. CCI, Comprehensive Complications Index; CKD, chronic kidney disease; eGFR, estimated glomerular filtration rate; EORTC QLQ-C30, European Organisation for Research and Treatment of Cancer Quality of Life Questionnaire Core 30; SF-36, 36-Item Short Form Survey Instrument; PCQ, participant costs questionnaire; PQ, participant questionnaire; QoR-15, 15-Item quality of recovery scale; T&T, time and travel questionnaire

### Sample size {14}

Our sample size is based on the primary outcome of kidney function, and is also adequate for a 90% power non-inferiority test on the CCI. We will have precision to describe positive surgical margins and quality of life:(i)For kidney function, we have used the width of the confidence interval between the groups in eGFR at 2 years: We estimate from systematic reviews that the absolute difference between PN and RN groups in arresting kidney function decline from baseline will be an eGFR of at least 10 ml/min/1.73m^2^, with a standard deviation of 16 [9, 19, 44]. This is a minimal clinically important difference informing international guideline recommendations for PN [45–48]. Based on the only randomised data available for PN vs RN, we predict a difference of at least 15 ml/min/1.73m^2^ at 2 years [3, 12]. As we require the confidence interval around the estimated difference to rule out a minimal clinically important difference of 10 ml/min/1.73m^2^, we have used a confidence interval of width 7. To be 90% sure our two-sided 95% confidence interval is at most 7, requires outcome data on 178 participants in each arm, or 356 participants in total. We will gain extra precision by using participants’ baseline eGFR in analysis.

We have inflated the sample size to account for 15% of potential attrition over 2 years to 420 randomised participants in total.

(ii)We require CCI outcome data on 380 procedures for 90% power to rule out a 4-point non-inferiority margin (i.e. we would tolerate up to 4 points higher CCI in the PN group) using the upper bound from a one-sided 97.5% confidence interval around the difference in means between the groups. The 4-point margin was derived using expert opinion and patient and public involvement on a non-inferiority margin for major complications, and from data on a minimally important difference in the CCI [32].(iii)With 420 procedures, we will have adequate precision to describe rates of positive surgical margin over a range of scenarios. Positive surgical margin rates up to 5% may be expected, with only < 1% requiring re-treatment [49].(iv)Our sample size also gives adequate power/precision to compare quality of life (expressed as area under curve analysis between randomisation and 24 months), with approximately 90% power to detect a third of standard deviation.

Based on Mayo Scoring System, rates of metastatic recurrence over 3 years for low-risk (most T1a/T1b) tumours are 2.1% [50]. In a contemporary series comparing PN with RN for T1b, 5-year metastases rates were 8.2% and 12.8%, respectively [51]. Nevertheless, survival rates for localised T1b renal cancer remain high with over 5-year cancer-specific survival rates for PN = 97.6% and RN = 95.5% [51]. Also, 2-year overall survival rates in the Van Poppell study were > 95% for both PN and RN [13]. Therefore, we do not anticipate any emerging patterns of differential outcome on the main measures of interest due to few events at 2 years.

For the process evaluation interviews, approximately 15 interviews per group will be conducted for participants who consented to the RCT and patients who did not consent to the RCT. A minimum of 15 clinical and recruitment staff at a minimum of 7 participating centres will also be interviewed. Sampling will be informed by Francis et al. [52]. All staff involved in discussing the PARTIAL trial with potential participants will be asked to routinely record consultations in which the trial is discussed.

### Recruitment {15}

Potential participants are identified following review by specialist MDT at UK hospitals. Potentially eligible patients may be identified in generalist urologist clinics in hospitals without specialist expertise in PN or RN. Such patients may be discussed at MDT meetings at specialist centres where their treatment may take place.

Local pathway and procedures at participating hospitals are different and the timing and mode of approach to eligible patients and the consent process may vary to accommodate both the local circumstances and the needs and preferences of the potential participant. A study poster may be displayed as a resource to support recruitment.

The embedded process evaluation aims to identify and address key challenges to trial recruitment and retention. It is modelled on the Quintet Recruitment Intervention [53] and augmented using a behavioural science approach to inform key components of data collection, analysis and development of feedback. The process evaluation includes the following: monitoring of participant flow at sites; audio-recording and analysis of trial consultations; and theory informed interviews with patients and site staff involved in the trial at a range of sites. The results of this evaluation are to be fed back to sites and included in ongoing site training events in real time to support and improve recruitment.

An embedded internal pilot phase with stop/go criteria will establish if recruitment is achievable.

## Assignment of interventions: allocation

### Sequence generation {16a}

Participants are randomly allocated using a remote central, computer-generated randomisation system accessed on the trial website (developed and administered by the Centre for Healthcare Randomised Trials (CHaRT), University of Aberdeen). The allocation algorithm uses centre, pre-operative eGFR (45–59; ≥ 60), tumour size (T1a; T1b), and pre-randomisation biopsy (yes; no) as minimisation covariates to allocate to PN or RN.

### Concealment mechanism {16b}

A remote, central, computer-generated randomisation system conceals the allocation sequence.

### Implementation {16c}

A delegated member of the local research team enrols the participant on the trial website. The remote, central, computer-generated randomisation system that is embedded on the trial website assigns the participant to either PN or RN.

## Assignment of interventions: blinding

### Who will be blinded {17a}

Participants and the local research team are informed which surgical intervention (PN or RN) has been allocated after randomisation. It is not possible to blind participants or the immediate clinical, nursing and research teams to the surgery they are receiving. However, both the kidney function and harms co-primary outcomes are determined objectively.

### Procedure for unblinding if needed {17b}

Not applicable—the trial is not blinded.

## Data collection and management

### Plans for assessment and collection of outcomes {18a}

Schedule of enrolment, interventions and assessments are summarised in Table 1.

**Table 1 Tab1:** Schedule of enrolment, interventions, and assessments

	**Trial period**								
	**Enrolment & allocation**	**Post-allocation**							
		**Surgery**	**Post-surgery**			**Post-randomisation**			
**Timepoint**	**R0**	**S0**	**S0 + 1 week**	**S0 + 1 month**	**S0 + 3 months**	**R0 + 6 months**	**R0 + 12 months**	**R0 + 18 months**	**R0 + 24 months**
**Enrolment:**									
Eligibility screen	X								
Informed consent	X								
Randomisation	X								
**Interventions:**									
Minimally invasive partial nephrectomy		X							
Minimally invasive radical nephrectomy		X							
**Assessments:**									
Baseline characteristics	X								
Renal function: eGFR^a^	X		X	X		X	X		X
Quality of life: EORTC QLQ-C-30, SF-36	X		X	X	X	X	X	X	X
Participant cost questionnaire	X					X	X	X	X
Participant time and travel							X		
Comprehensive Complications Index					X				
Quality of recovery: QoR-15			X	X	X				
Late complications						X	X	X	X
Cardiovascular events									X
Recurrence^b^									X
Further treatment									X
Surgical details & resource use		X							
Pathology & positive surgical margins		X							
Patient acceptability					X				

*eGFR* estimated glomerular filtration rate, *EORTC QLQ-C30* European Organisation for Research and Treatment of Cancer Quality of Life Questionnaire Core 30,
*QoR-15* 15-Item quality of recovery scale, *R0* date of randomization, *SF-36* 36-Item Short Form Survey Instrument, *S0* date of surgery

^a^There are preferable measurement windows for eGFR at key timepoints: 1 week post-surgery (within 1 week of surgery); 1 month post-surgery (± 1 week); 6 and 12 months post-randomisation (± 1 month); 24 month post-randomisation (± 3 months). All eGFR tests, including out of window observations, are recorded

^b^This outcome is not collected in participants who do not have confirmed renal cell carcinoma (RCC)

At baseline, the local research team captures baseline demographic and clinical information, including baseline renal function (eGFR) and tumour size and surgeon assigned location parameters (for PADUA classification [21]). Participants are asked to complete a baseline questionnaire prior to randomisation. During follow-up, the local research team collects outcomes from participant medical notes.

Renal function measurements (eGFR) are collected at key trial timepoints: at 1 week and 1 month post-intervention, and at 6, 12, and 24 months post-randomisation. The preferable window for the 1-week measurement is within 1 week of surgery. The preferable window for the 1-month measurement is ± 1 week. The preferable window for the 6- and 12-month measurements is ± 1 month. The preferable window for the 24-month measurements is ± 3 months. Where these key trial timepoints do not coincide with eGFR measurements taken as standard of care, the local research team requests that the eGFR measurement is taken either at a hospital outpatient clinic or in primary care. The results of all eGFR tests post-randomisation, up to 24 months post-intervention, including out of window observations, are recorded by the research team from laboratory records. Serum creatinine values are collected and will be used to calculate eGFR centrally for analysis.

PQs at 1 week, 1 month and 3 months post-intervention, and 6, 12, 18 and 24 months post-randomisation are administered by the trial office. Questionnaires are completed by the participant either electronically (with a link sent by email or text) or as a hardcopy (in the post with a reply-paid envelope provided), in accordance with their preference. Up to two reminders are sent to participants. The final reminder is by telephone. If there is no response by telephone, the final reminder is sent by post. The 1-week questionnaire is excluded from the final postal reminder due to potential overlap with the 1-month questionnaire.

For the process evaluation component, the number of participants screened, eligible, approached and randomised is recorded on clinic logs. All staff involved in discussing the trial with potential participants are asked to routinely audio-record consultations in which the trial is discussed. Semi-structured telephone interviews are conducted with participants who consented to the RCT, patients who did not consent to the RCT, and clinical and recruitment staff at participating centres.

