### Outcomes {12}

Co-primary outcome measures:
(i)Gains in preserving renal function as measured by eGFR (using the Chronic Kidney Disease Epidemiology Collaboration (CKD-EPI) 2009 formula without the race coefficient as recommended by the National institute for Health and Care Excellence, the UK Kidney Association and European Federation of Clinical Chemistry and Laboratory Medicine [29–31]). The adjusted mean difference between the eGFR score in the PN and RN groups will be analysed to determine if PN results in better maintenance of eGFR compared with RN. This co-primary outcome timepoint is at 2 years post-randomisation, and it will be possible to present effect sizes at all follow-up points using a repeated measures model.(ii)Harms captured by Comprehensive Complication Index (CCI). The CCI is validated in renal surgery [32, 33] and based on the Clavien-Dindo classification (reporting on the most severe event) and is calculated as the sum of all surgical complications that are weighted for their severity [34]. Ideally, the CCI will be analysed as an adjusted mean difference between the PN and RN groups, but the distribution or heteroscedasticity may require a different analysis. This co-primary outcome timepoint is reported at 3 months post-intervention (i.e., collecting events over the peri-operative period after skin closure for the index procedure to three months after surgery).

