### Plans to promote participant retention and complete follow-up {18b}

The process evaluation team will identify and address the key challenges to retention from the perspective of overall acceptability. Participant flow at sites, recruitment consultations, and interviews with patients and site staff will be analysed. Potential solutions in the form of action plans will be developed, implemented and evaluated on a rolling case basis.

Participants are sent up to two reminders to complete the follow-up questionnaires. First attempts and first reminders are emailed, posted or texted to participants, in accordance with their preference. The final reminder is attempted by telephone. If there is no response by telephone, the final reminder is sent by post. If questionnaires are returned as non-deliverable, attempts will be made by site staff or the trial office to trace the participant. Questionnaires are administered to all participants who were randomised in the trial, regardless of whether they had the surgery they were allocated, unless they have withdrawn from questionnaire follow-up.

Preferable measurement windows for the key eGFR measurements are specified within the protocol. An out of window measurement is preferable to no measurement at any timepoint. Therefore, all eGFR tests post-randomisation up to 24 months post-intervention, including out of window measurements, are collected and will be incorporated into the analysis.

All other outcomes are collected from the participant’s medical records, unless the participant has specifically withdrawn consent for collection of outcome data.

Participants are followed up for trial outcomes unless they have withdrawn from all aspects of the trial. All data collected up to the point of complete withdrawal from the trial is retained and used in the analysis. Participants for whom any outcome data are available are included in an intention to treat analysis.

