### Adverse event reporting and harms {22}

In PARTIAL, serious adverse events (SAEs) are recorded between commencement of surgical treatment (entering the anaesthesia suite) until the participant exits from the trial (24 months after randomisation or withdraws from collection of data). The investigator queries relevant SAEs at every visit and within follow-up questionnaires. SAEs must be serious and related to the research procedures required by the protocol. SAEs do not include procedures administered as standard of care, complications of surgery, prolongation of hospitalisation without an associated adverse event, additional medication required above that normally expected, emergency presentations and admissions, routine admissions for pre-planned events, or any adverse event that would be captured as a secondary outcome for the trial. Complications and secondary outcomes are captured in case report forms and PQs. The investigator (or medically qualified delegate) reviews medical documentation related to the event, completes the SAE form and reports to the trial office within 24 h of knowledge of the event. If a potential SAE is recorded on a PQ, the trial office will seek further information from the investigator team. The investigator, medically qualified delegate or chief investigator assess the seriousness, relatedness and expectedness of the event. The trial office notifies unexpected SAEs to the sponsor within 24 h of receipt of a signed SAE notification. The chief investigator or delegate notifies unexpected SAEs to the research ethics committee within 15 days of the chief investigator becoming aware of the event. The trial oversight committees and funder review all SAEs in regular progress reports.

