## Trial status

The current protocol is version 3, 01 August 2024. The first participant was recruited into the trial on 18 April 2023. Recruitment was initially expected to complete 31 December 2024 with last participant follow-up expected in December 2026. The funder is supportive of an overall extension to the trial with a revised recruitment end date of 30 September 2026 and last participant follow-up expected in September 2028.

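### The cut-off for recording eGFR is counted from surgery, but the co-primary 2-year window is counted from randomisation, so recording can stop before the window closes

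*Protocol article*

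**What the plan says.** **The timepoint** is fixed on the randomisation clock. Outcomes {12} says: "This co-primary outcome timepoint is at 2 years post-randomisation". Plans for assessment and collection of outcomes {18a} schedules eGFR "at 1 week and 1 month post-intervention, and at 6, 12, and 24 months post-randomisation", and adds: "The preferable window for the 24-month measurements is ± 3 months".

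**The recording rule** is on the surgery clock. The same section says: "The results of all eGFR tests post-randomisation, up to 24 months post-intervention, including out of window observations, are recorded". Plans to promote participant retention and complete follow-up {18b} repeats the limit and extends it to the analysis: "all eGFR tests post-randomisation up to 24 months post-intervention, including out of window measurements, are collected and will be incorporated into the analysis". That section also holds that a value outside the window is better than none.

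**Footnote a to Table 1** gives a rule with no end date: "All eGFR tests, including out of window observations, are recorded".

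Three other places bear on the point:
- Criteria for discontinuing or modifying allocated interventions {11b} allows that surgery may not take place and keeps such participants in follow-up.
- Adverse event reporting and harms {22} records serious adverse events "until the participant exits from the trial (24 months after randomisation or withdraws from collection of data").
- Trial status gives "a revised recruitment end date of 30 September 2026 and last participant follow-up expected in September 2028".

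**The concern.** A recording cut-off should fall no earlier than the end of the window it serves. Here the two are measured from different origins. Whether the cut-off covers the window depends on how long each participant waits for surgery, which the article does not state.

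A site that follows {18a} to the letter would leave out a creatinine result already in the laboratory record if it fell after 24 months from surgery, even when it lay inside the 24-month window. That runs against the stated preference in {18b} for a late value over a missing one. For a participant who is never operated on, the rule gives no stopping date at all.

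The outcome affected is the co-primary that sets the sample size, and the allowance for missing 2-year values is almost fully used by the planned 15% attrition.

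**Working it through.** **1. The plan's own figure (Sample size {14}).** Inputs: SD 16, two-sided 95% interval of full width at most 7 (half-width 3.5), 90% assurance, 15% attrition. Find the smallest n per arm with

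P( t(0.975, 2n−2) × S × √(2/n) ≤ 3.5 ) ≥ 0.90, where S² is distributed as 16² × χ²(2n−2)/(2n−2).

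This gives n = 178 per arm (assurance 0.908), or 356 in total, as stated. Then 356/0.85 = 418.8, so 419 against the stated 420. In the other direction, 420 × 0.85 = 357, one more than needed.

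**2. Both rules on the randomisation clock.** Let d be the months from randomisation to surgery.
- Window: 24 − 3 = 21 to 24 + 3 = 27 months.
- Recording ends at 24 + d months.
- Part of the window left uncovered: max(0, 27 − (24 + d)) = max(0, 3 − d) months.

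The article gives no value for d, so the values below are assumptions that show the range:

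| d (months, assumed) | Recording ends (month) | Window uncovered (months of 6) |
|---|---|---|
| 0 | 24 | 3 |
| 1 | 25 | 2 |
| 2 | 26 | 1 |
| 3 or more | 27 or later | 0 |

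Because surgery follows randomisation, d is never negative, so results up to month 24 are captured for anyone operated on. Table 1 places the 3-month post-surgery column before the 6-month post-randomisation column. That order would fit surgery within about 3 months of randomisation, but a column order is not a stated delay.

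**3. No surgery.** If the operation does not take place, d does not exist and the cut-off has no date, although follow-up continues.

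**4. The Table 1 footnote.** It covers every eGFR test and sets no limit. It therefore differs from {18a} and {18b} for any test after month 24 + d.

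**5. What a loss would cost, for illustration only.** If an assumed share of the 357 participants had no 2-year value for this reason, the assurance that the interval is no wider than 7 would be:

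| Assumed further loss | Evaluable | Assurance |
|---|---|---|
| 0% | 357 | 0.91 |
| 2% | 349.9 | 0.86 |
| 5% | 339.1 | 0.74 |
| 10% | 321.3 | 0.48 |

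These use the unadjusted SD of 16. The planned baseline adjustment would offset part of the fall. Nothing in the article says which row applies, or that any loss will occur.

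**6. Calendar.** A participant randomised on 30 September 2026 reaches month 24 at the end of September 2028 and month 27 at the end of December 2028. Recruits from July to September 2026 have windows that close in October to December 2028.

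**The case against.** The strongest reply is that {18a} first schedules the 24-month measurement with its own window, and only then adds that tests up to 24 months after surgery are taken from laboratory records. On that reading the sentence widens capture to routine tests and does not limit the scheduled one. The footnote supports this, and nowhere is an in-window value said to be dropped. Sites also request a test when routine care does not supply one, which should draw values towards month 24. Someone with an earlier in-window result keeps a usable value. The repeated-measures model also uses participants who lack the 24-month measurement. Finally, an article may leave retrieval rules to the full protocol.

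Much of this stands, and it means that loss of data is a risk and not a fact. It does not remove the mismatch. Both {18a} and {18b} apply the limit to all eGFR tests, out-of-window ones included, and {18b} applies it to the analysis as well. The point concerns a rule the article states, not detail it omits.

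A reader might infer more, in three ways that the document does not support:
- **That the primary outcome has three different end points.** Its timepoint is 24 months after randomisation throughout; only the limit on data capture varies.
- **That eGFR collection ends when the participant exits at 24 months.** That exit is stated to bound serious adverse event recording. Half the window would be uncovered for everyone only if it were carried over to eGFR.
- **That the September 2028 date cuts off the last recruits.** It is an expected milestone, and each of them can have an in-window test by then.

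**Conclusion.** The concern holds as an inconsistency in a stated rule. Taken literally, eGFR recording stops before the 21 to 27 month window closes for anyone operated on less than 3 months after randomisation, by 3 − d months. It also conflicts with the Table 1 footnote and is undefined where surgery does not proceed. Some in-window values, and some late values that {18b} would rather have than not, may be missed.

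The number missed cannot be derived. It is tempting to turn the uncovered months into a rate: 2/6 = 33% at a 1-month wait, 1/6 = 17% at 2 months. Those are shares of the window under an assumed delay and an even spread of test dates, not shares of participants without an outcome. At a delay of 3 months or more the gap is zero.

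The sample size is unaffected: 178 per arm reproduces. The reason to act is that the margin is one participant (357 against 356) and the correction costs very little.

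**What to change.** - In {18a} and {18b}, replace the surgery-based limit with one rule on the randomisation clock: all eGFR results to at least 27 months post-randomisation, for every randomised participant whether or not operated on.
- Give footnote a to Table 1 the same limit.
- State that the 24-month exit in Adverse event reporting and harms {22} applies to serious adverse event recording and not to eGFR capture.
- For the last recruits, either let final eGFR capture run to the end of their window (December 2028) or schedule their test by month 24.

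With this rule the uncovered part of the window is 0 months for every value of d. No visit is added and 420 randomised is unchanged. The cost is a minor amendment and, for the last recruits, up to 3 more months of laboratory-record lookup.
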